The optimal initial oxygen concentration for stabilizing infants after birth is still a subject of debate, as both hypoxia and hyperoxia can cause damage of multiple organ systems (16, 17). Hypoxia may lead to delayed cellular damage, (18) as during hypoxia the production of free radicals will be provoked, by an elevated level of hypoxanthine (19). On the other hand, high oxygen levels increase the biosynthesis of prostaglandins which are an additional mechanism inhibiting chemoreceptors in the respiratory center (20). In addition, free radical production (associated with both oxidative and nitrosative stress) increases during hyperoxia, which can overwhelm the relatively immature antioxidant capacity of the preterm infant. The resulting excess of free radicals cause wide-spread damage to cells, enzymes, lipids, DNA, and proteins (21–24).

The recent meta-analysis of Oei et al. showed a higher mortality rate in the group of preterm infants (< 32 weeks of gestation) resuscitated with an initial FiO_2_ of 0.21 compared to the group resuscitated with an initial FiO_2_ of 1.0 (18). Furthermore, when stabilization of preterm infants after birth was started with low oxygen concentrations (FiO_2_ 0.21–0.3), oxygen saturation (SpO_2_) and heart rates increased more slowly than the SpO_2_ references outlined in the international guidelines, despite the use of respiratory support. This indicates that when starting respiratory support with lower oxygen concentrations preterm infants are at a higher risk for hypoxia (25). Indeed, this was shown in the study of Goos et al. (12) and White et al. (13).

Regardless of the initial FiO_2_ level, in all studies most infants ended up with a FiO_2_ between 0.4 and 0.6 after 5 min to reach SpO_2_ target ranges. Currently, to prevent hyperoxia and achieve normoxia in newborns, international guidelines recommend to start stabilization after birth in preterm infants with low FiO_2_ (0.21–0.3) (26), after which FiO_2_ should be titrated based on SpO_2_ target ranges (16, 17, 27). In this recommendation, a period of low oxygen saturation is accepted and the effect of hypoxia on respiratory effort seems to be disregarded (28).

We hypothesize that with an initial FiO_2_ of 1.0, infants will reach SpO_2_ target ranges more rapidly, leading to less hypoxia and an increase in respiratory effort. With careful titration of FiO_2_ based on SpO_2_ target ranges, we hypothesize that the occurrence of hyperoxia will be minimized.

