### (Serious) Adverse Events

Adverse events are defined as any undesirable experience occurring to a subject during the study, considered related to the initial FiO_2_ setting of 1.0. All adverse events observed by the investigator or the staff will be recorded and noted to the medical ethical committee of the LUMC.

This study population (preterm infants) has a high risk of serious complications, which are inherent to their vulnerable condition and unrelated to the intervention that is under evaluation in this trial. These complications (pneumothorax, bronchopulmonary dysplasia (BPD), retinopathy of prematurity (ROP), IVHs grade 3 or more, cystic periventricular leukomalacia (PVL), necrotizing enterocolitis (NEC) grade 2 or more, death) are not expected to be related to the intervention (starting stabilization after birth with a FiO_2_ of 1.0 vs. 0.3) as the intervention will be performed only at the start of stabilization, after which in both groups titration will be performed. In light of the above, immediate and individual reporting of all these conditions related complications will not enhance the safety of the study, and therefore these complications will be handled as adverse events.

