## Discussion

Most preterm infants need additional oxygen during stabilization at birth to achieve appropriate SpO_2_ target ranges (34). Results of a recent meta-analysis demonstrated that persisting hypoxia at 5 min after birth is associated with a higher risk of mortality and the development of an intraventricular hemorrhage, which we should try to avoid (14). Although a recent systematic review showed no differences in percentage of infants achieving SpO_2_ target ranges between infants initiating stabilization with high or low FiO_2_, the level of evidence of these results is low (35). It is therefore still unclear whether the initial FiO_2_ level influences breathing effort, thereby influencing the capacity of preterm infants to reach the target range. However, it has recently became clear that oxygenation can only be influenced in infants supported by non-invasive ventilation in case of presence of spontaneous breathing, as then the larynx opens and an open airway is achieved (9). Before focusing on achievement of SpO_2_ target ranges, we should look at the effect of initiation stabilization with a high FiO_2_ on breathing effort.

The current SpO_2_ target ranges used during stabilization at birth are based on the reference values described by Dawson et al. (27). While these target ranges have been based on data from healthy term and preterm infants, those values might not apply to infants requiring more respiratory assistance at birth. In the current resuscitation guidelines, oxygen titration is recommended if infants fail to achieve the 25th centile of the SpO_2_ reference ranges and are thus hypoxemic in the first minutes after birth (14, 36). Because hypoxia is known to provide inhibitory input into the respiratory center, this effect on respiratory effort has been overlooked with regard to the importance of oxygen titration. It is possible that the compromised preterm infant requiring respiratory support during transition would benefit by higher SpO_2_ reference ranges during stabilization at birth. By initiating stabilization at birth with a FiO_2_ of 1.0, we hypothesize that infants will achieve higher SpO_2_ values in the first minutes after birth, leading to an increase in respiratory effort at birth.

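### Prompt individual reporting of death and severe IVH is waived on a ground that conflicts with the protocol's own background

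*Protocol article*

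**What the plan says.** The section (Serious) Adverse Events of the protocol article lists seven complications: pneumothorax, bronchopulmonary dysplasia, retinopathy of prematurity, and "IVHs grade 3 or more, cystic periventricular leukomalacia (PVL), necrotizing enterocolitis (NEC) grade 2 or more, death". It calls them "inherent to their vulnerable condition and unrelated to the intervention that is under evaluation in this trial". The reason given is that no relation is expected, "as the intervention will be performed only at the start of stabilization, after which in both groups titration will be performed". From this it concludes that "immediate and individual reporting of all these conditions related complications will not enhance the safety of the study", and it handles the complications as adverse events instead.

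The same section defines adverse events as experiences "considered related to the initial FiO_2_ setting of 1.0", and says that all those observed "will be recorded and noted to the medical ethical committee of the LUMC". It gives no timing for that notification.

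Elsewhere, the Introduction cites a meta-analysis that "showed a higher mortality rate in the group of preterm infants" started on FiO2 0.21 compared with those started on 1.0. The Discussion cites another in which "persisting hypoxia at 5 min after birth is associated with a higher risk of mortality and the development of an intraventricular hemorrhage". The section Other Outcomes lists pneumothorax, IVH grade 3 or more and neonatal death among the short-term outcomes to be recorded.

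**The concern.** The waiver rests on a stated reason, and that reason is at odds with the evidence used to justify the trial. The article randomises the starting FiO2 because it may change early hypoxia and breathing effort, and it cites early hypoxia and the starting FiO2 itself in connection with death. It then drops prompt reporting of death because the starting FiO2 is said to be unrelated to it.

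What is at stake is oversight during recruitment. The arms are expected to differ in early oxygenation, and under Recruitment and Consent some infants are randomised before their parents can be asked. Nothing in the adverse-event section requires a death or a severe IVH to reach the ethics committee as an individual case while further infants are being enrolled.

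**Working it through.** The main check sets passages side by side. Arithmetic only sizes the reporting burden.

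**Step 1: does the starting FiO2 bear on death, on the article's own account?** The adverse-event section says no. The Introduction cites a mortality difference in which the exposure is the initial FiO2 (0.21 against 1.0). The article gives no rates.

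**Step 2: does later titration remove the link?** The adverse-event section relies on this. The Introduction says that in all studies most infants reached FiO2 0.4 to 0.6 after 5 min, whatever the starting level. Taken at face value, convergence by 5 min was compatible with a mortality difference. The article does not say that these are exactly the studies pooled in the meta-analysis. If they are not, this step weakens, but step 1 stands.

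**Step 3: is there a pathway through hypoxia?** The Introduction hypothesises that starting at 1.0 leads to less hypoxia. The Discussion associates hypoxia persisting at 5 min with mortality and IVH. Together they connect the randomised factor to two of the listed complications, by hypothesis for the first link and by association for the second.

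**Step 4: what still happens to these events?** They are handled as adverse events and noted to the ethics committee, and neonatal death and IVH grade 3 or more are recorded outcomes. What is removed is the prompt, case-by-case report. The adverse-event definition refers only to the 1.0 setting, whereas the mortality evidence in the Introduction lies on the low-oxygen side. A remedy should therefore name both arms.

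**Step 5: the burden.** The only planned figure used is 50 infants (Sample Size Calculation). It reproduces with a difference of 60, SD 70, two-sided 5% and 80% power:

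- n per arm = 2 × (1.960 + 0.842)² × 70² / 60² ≈ 21.4, so 22.
- Allowing 10% loss: 22 / 0.90 = 24.4, so 25 per arm and 50 in total.

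The documents give no mortality rate. Assuming 5% to 15%:

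- 0.05 × 50 = 2.5 deaths.
- 0.15 × 50 = 7.5 deaths.

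Severe IVH cases come on top and are not sized here.

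**Step 6: could the final comparison stand in for individual review?** With 25 per arm, the smallest splits with Fisher's exact p < 0.05 are 0 against 6 (p = 0.022), 1 against 7 (p = 0.049) and 2 against 9 (p = 0.037). Under assumed event rates the power is:

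| Rates | Power |
|---|---|
| 5% vs 10% | 1% |
| 5% vs 15% | 7% |
| 10% vs 20% | 9% |
| 10% vs 30% | 31% |

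A formal end-of-trial test would probably miss a moderate imbalance. This agrees with Other Outcomes, which says that the study is not designed to show differences in clinical outcomes.

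**The case against.** The strongest reply is that the cited background does not refute the judgement that no relation is expected.

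- The mortality evidence used 0.21, and the article treats 0.3 as materially different: Sample Size Calculation halves the expected effect for that reason.
- The IVH link is an association, and no grade is given, whereas the waiver concerns grade 3 or more.
- The Discussion also cites a systematic review that found no difference in reaching SpO2 targets between high and low starting FiO2, though it rates that evidence as low.

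All of this stands and limits the strength of the point. It does not rescue the stated reason. An open question about a link with mortality is not a basis for declaring deaths unrelated in advance.

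A reader might go further and infer that deaths and severe hemorrhages would be seen by nobody during recruitment, or that those in the 0.3 arm would never be reported. The documents do not support this. The section expressly handles the listed complications as adverse events and sends adverse events to the ethics committee, and Other Outcomes records both events. Nor does the article's silence on a safety board, notification timing or by-arm review show that these are absent, because a condensed article commonly leaves such details to the full protocol. The point rests on a rule and a reason that the article states.

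It is also fair to say that so few events cannot settle an arm difference. That argues against a formal by-arm look partway through, where any cut point would be arbitrary. It does not argue against prompt review of each case.

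**Conclusion.** The point holds in a limited form. The reason given for waiving prompt individual reporting of death and IVH grade 3 or more conflicts with the Introduction and the Discussion, and these passages must be reconciled. The consequence is that no prompt individual report is required for the two listed events that the background connects with early hypoxia. For death, the background also points to the starting FiO2 itself.

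The conclusion assumes that the adverse-event section means what it says about the waiver. It needs no assumption about event rates; the range of 5-15% serves only to show that the burden is small. The sample size, the power and the primary analysis are unaffected. A waiver for complications common in this population might be defended on other grounds, but the ground stated does not carry it for these two events. The change should be made because it is cheap and concerns safety.

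**What to change.** In (Serious) Adverse Events, for death and IVH grade 3 or more:

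1. Remove the statement that they are unrelated to the intervention, and the statement that reporting them individually would not enhance safety.
2. Require each such event, in either arm and irrespective of judged relation, to be reported individually and promptly to the ethics committee with the allocated arm.
3. Leave the waiver in place, if wished, for the other five listed complications. No by-arm listing during recruitment is needed.

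The cost is a change of wording and a few extra reports: the 2.5 to 7.5 expected deaths under the assumed range, plus the severe IVH cases. Both events are already recorded as outcomes, so no new data collection or staff is needed.

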### Statistical Analysis

Data will be presented as median [interquartile range (IQR)], mean ± standard deviation (SD) or number (percentage) where appropriate. Data will be checked for meeting the assumption of normality first by making a frequency distribution per minute. Outliers will be identified and handled according to the data (outliers will be deleted if there are arguments to do so, or transformed if not). Intention-to-treat will be employed. Statistical analysis will be performed with SPSS software version 23.0 (SPSS, Chicago, Illinois; 2012).

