## Treatment of Subjects

### Randomization

Allocation will be stratified by gestational age. Infants of 24^+0^-26^+6^ weeks and 27^+0^-29^+6^ weeks will be included using variable block (4–6) sizes. Concealment of allocation will be ensured by using the randomization process of Castor EDC (Amsterdam, The Netherlands), an electronic data capture system. The neonatal fellow or neonatal consultant in charge of the procedure will randomize using Castor EDC.

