### Study Procedures

Infants will be randomized to start stabilization after birth with an initial FiO_2_ of either 1.0 or 0.3, after which FiO_2_ will be titrated following target SpO_2_ recommended in our local guidelines on stabilization after birth, which are based on the target ranges described by Dawson et al. (27). In both groups, all other procedures in the delivery room and NICU will be performed according to the local and international guidelines, only the initial FiO_2_ setting will be different. Cord clamping will be performed after 30 s in case of an apneic infant, and after 60 s if the infant is breathing at birth.

After the initial FiO_2_ setting, titration will be performed according to the local protocol:

-When SpO_2_ is below target ranges defined by Dawson et al. FiO_2_ will be titrated up to 0.5 and subsequently to 1.0, when the initial FiO_2_ setting was 0.3. In case of an initial FiO_2_ setting of 1.0, FiO_2_ will be maintained at 1.0.-When SpO_2_ is above target ranges, FiO_2_ will be titrated down to 0.5 and subsequently to 0.3 and 0.21. If SpO_2_ is above target ranges when stabilization is initiated with FiO_2_ 0.3, FiO_2_ will be titrated down to 0.21 directly.

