To record SpO_2_ and heart rate a Masimo SET pulse oximeter probe (Masimo Radical, Masimo Corporation, Irvine, California, USA) or Nellcor^TM^ pulse oximeter probe (Covidien, Dublin, Ireland) is placed around the right wrist or hand of the infant. The FiO_2_ is measured using a portable oxygen analyzer AX300-I (Teledyne Analytical Instruments, CA, USA), and the airway pressures are registered by a variable orifice flow sensor (Avea Varflex Flow Transducer, Carefusion, Yorba Linda, CA, USA) connected to the facemask measuring the flow in and out the infant. The signals are digitized at 200 Hz using the NewLifeBox-R physiological recording system (Advanced Life Diagnostics, Weener, Germany) and all signals are recorded by the NewLifeBox Neo-RSD computer system (Advanced Life Diagnostics, Weener, Germany) supported by Polybench physiological software (Applied Biosignals, Weener, Germany). Pulmochart software (Applied Biosignals, Weener, Germany) is used to analyze primary and secondary outcomes.

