#### Statistical Analysis of Primary Outcome

Differences in average respiratory minute volume in the first 5 min after birth between the study groups will be tested with a Student's *t*-test if the data are found to be parametric, or with Mann-Whitney u-test when the data are non-parametric.

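### The outlier rule lets primary-outcome values be deleted or transformed at discretion once the data are seen, which can inflate type I error

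*Protocol article*

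**What the plan says.** All of the following is in the protocol article.

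- **Statistical Analysis, timing of the decision.** "Outliers will be identified and handled according to the data". The rule itself is that "outliers will be deleted if there are arguments to do so, or transformed if not". The next sentence is "Intention-to-treat will be employed".
- **Statistical Analysis, data check.** "Data will be checked for meeting the assumption of normality first by making a frequency distribution per minute". The article does not say whether the unit that may be deleted is a breath, a minute or an infant.
- **Statistical Analysis of Primary Outcome.** Average minute volume is compared with a "Student's *t*-test if the data are found to be parametric, or with Mann-Whitney u-test when the data are non-parametric".
- **Randomization.** "The neonatal fellow or neonatal consultant in charge of the procedure will randomize using Castor EDC".
- **Study Procedures.** For an infant below the saturation target, titration depends on the starting setting: "In case of an initial FiO_2_ setting of 1.0, FiO_2_ will be maintained at 1.0".
- **Measurement of respiratory function.** FiO2 is measured alongside flow, and "all signals are recorded by the NewLifeBox Neo-RSD computer system".

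The article does not use the words open-label, blinded or masked, and does not say whether the person scoring traces or analysing data knows the arm.

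**The concern.** This is a stated rule, not a detail left open. An extreme value is either deleted, on grounds settled after the data are inspected, or transformed. No third branch leaves a valid extreme alone.

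The hypothesis is that less hypoxia means more breathing effort. A nearly apnoeic or a very vigorous infant is therefore part of the signal, and at this sample size one or two infants can move the result. If removal is done arm by arm, or chosen with the result in view, the test no longer has its nominal error rate. If a randomised infant's valid value is dropped, the analysis is no longer by intention to treat.

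**Working it through.** **1. Inputs (Sample Size Calculation).** Control mean 150, SD 70, difference 60 mL/kg/min (150 to 210), two-sided 5%, power 80%, 22 per arm, 10% allowance, 50 in total.

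**2. The plan's own figure.**
- n per arm = 2 × [70 × (1.960 + 0.842) / 60]² = 21.4, rounded up to 22. This reproduces. The t-based solution is 22.4, a trivial difference.
- 22 / 0.90 = 24.4, rounded up to 25 per arm, or 50 in total. This reproduces.

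**3. Simulation set-up.** No treatment effect, 22 per arm, mean 150, SD 70, t-test at two-sided 5%, 10,000 runs. The outcome is normal, or lognormal with the same mean and SD: log-scale variance ln(1 + (70/150)²) = 0.197, log-scale mean ln 150 − 0.197/2 = 4.912. The Monte Carlo standard error at 5% is √(0.05 × 0.95 / 10,000) = 0.2 percentage points. **Every outlier rule below is an assumption, because the article gives none.**

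| Assumed handling | Type I error, normal | Type I error, lognormal |
|---|---|---|
| All values kept | 5.2% | 4.8% |
| 1.5 IQR deletion, pooled data, arm ignored | 5.4% | 5.2% |
| 2 SD deletion, pooled data, arm ignored | 5.5% | 5.4% |
| 1.5 IQR deletion within each arm | 8.7% | 12.2% |
| 2 SD deletion within each arm | 10.3% | 9.8% |
| Smallest p among keep all, pooled deletion, transform | 6.9% | 8.0% |
| Smallest p when at most one extreme value may be dropped | 12.2% | 12.6% |

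A separate run of 20,000 gave 8.1% / 11.8% for within-arm 1.5 IQR deletion and 4.8% / 4.9% for a fixed pooled rule, so the pattern is stable.

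**4. Why pooled and within-arm deletion differ.** A rule that looks only at the pooled values leaves the arm labels exchangeable under no effect, so the comparison of what remains is still fair. A rule centred on each arm's own values trims the spread that the t-test uses as its yardstick, so chance differences between arms look too large.

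**5. How often the rule would bite.** With 1.5 IQR fences within arm, at least one value is flagged in 53% (normal) or 83% (lognormal) of simulated trials with no effect.

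**6. Worst case.** Removing one value per arm, the lowest in one and the highest in the other, shifts the difference by 12.7 mL/kg/min, or 12.7/60 = 21% of the planned effect. Type I error is then about 11%.

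**7. Power.** Losing two infants per arm (22 to 20) lowers t-test power from 79.3% to 75.2%.

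**The case against.** Several stronger readings are tempting, and the document does not support them.

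- **That deletion inflates type I error however it is done.** It does not. A fixed rule on pooled data, blind to arm, keeps about 5%. The inflation comes from deleting within arm or from choosing with the result in view. The supportable statement is that the rule *can* inflate the error.
- **That the simulated rates describe this plan.** They do not. No cutoff, unit or frequency of deletion is given. The 21% shift assumes deliberately one-sided removal, which nothing in the article suggests.
- **That the rule contradicts intention-to-treat outright.** Data are checked minute by minute, and the section on respiratory function recognises mask leak as part of the measurement. The unit removed may be a breath or a segment, in which case no randomised infant is lost. The conflict is conditional.
- **That the analyst is unblinded.** The bedside team must know the setting, and the recording system holds FiO2 with the other signals, so allocation could be visible to whoever scores a trace. That it will be is an inference, and analyst blinding may be covered in a fuller document.
- **That only the outlying values would be transformed.** The sentence attaches the word to the outliers, but coming after a normality check it may mean the whole variable.

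It can also be said that Mann-Whitney is available and limits the pull of extremes. That helps only in part: after within-arm 1.5 IQR deletion it still gives 7.7% (normal) and 8.9% (lognormal).

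Finally, an article condenses a fuller protocol, and lists of artefact criteria usually sit elsewhere. That excuses missing detail. It does not excuse a rule that the article states and that permits deletion on unspecified grounds.

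**Conclusion.** The point holds in this limited form. The article fixes a discretionary, data-dependent rule for the primary outcome. The rule is not confined to measurement artefact, is not declared blind to allocation, and has no branch that keeps a valid extreme value as observed.

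Under the assumed within-arm rules at 22 per arm, type I error with a t-test is about 9 to 12% instead of 5%. Under an arm-blind pooled rule it stays at about 5%. The size therefore depends on how the discretion is used, which the article does not say. The conflict with intention-to-treat arises only if a randomised infant's valid outcome is removed. The figures also assume outcomes that are normal or lognormal with the planned mean and SD.

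**What to change.** Replace the outlier sentence in Statistical Analysis with text to this effect:

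> *Breaths or recording segments are excluded only for technical reasons listed in advance, judged without knowledge of allocation (for example with the FiO2 channel hidden). Every infant with a valid recording stays in the primary analysis with the observed value. Any transformation is chosen in advance and applied to all values. The primary result is reported with and without the exclusions.*

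This names the unit, removes the open-ended grounds for deletion, and makes the intention-to-treat statement hold among infants with a valid recording.

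The cost is a change of wording and slightly more work in scoring traces. Genuine extremes stay in the data and may widen the confidence interval. No extra infants are needed, and the sample size calculation is unchanged.
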